## Abstract

**Background:**

In oncology, detection and tracking of adverse events are of top priority and rely mostly on the Common Terminology Criteria for Adverse Events (CTCAE). Besides, clinical trials use as well patient-reported outcomes (PROs) to assess those adverse events, which are only accessible through patient self-reporting, such as fatigue, pain, and sleep disorders. Especially those issues that are not visible from the outside are often misinterpreted and underestimated by mere provider ratings. This trial aims at evaluating the impact of providing PRO data to providers on the accuracy of adverse event assessment in terms of inter-rater reliability of CTCAE ratings.

**Methods:**

The trial uses a cross-sectional, unblinded, randomized controlled trial design with two trial arms and a single assessment time point. Eligible patients (aged 18 and above, any cancer diagnosis, currently under treatment, inpatient or day clinic setting, present symptom burden, no psychiatric or mental problems, written informed consent) complete an electronic version of the EORTC QLQ-C30 and 16 additional questions taken from the EORTC Item Library. PRO data is immediately processed and made available to CTCAE rating providers for conducting their ratings during the medical encounter. Patients are randomly assigned 1:1 to the intervention group (providers see PRO results on the same screen as the CTCAE rating) and the control group (no access to PRO data during the CTCAE rating). A superiority analysis will compare the inter-rater reliability (using intra-class correlation (ICC) coefficients) between the control and the intervention groups for each adverse event evaluated.

**Discussion:**

The presented trial will demonstrate potential benefits of using PRO measures to improve the reliability of CTCAE ratings in cancer trials and the identification of adverse events. The new insights gained may lead to a new strategy for evaluating adverse events in clinical trials by combining patient and provider ratings. This might also have implications for daily clinical practice and cancer registries.

**Trial registration:**

ClinicalTrials.gov NCT04066868. Registered on August 26, 2019. Competence Center for Clinical Trials of the Medical University of Innsbruck 20190513-2007. Registered on May 14, 2019. (version 6.0, March 18, 2019)

## Background

In oncology, the Common Terminology Criteria for Adverse Events (CTCAE) (developed by the US-American National Cancer Institute (NCI) of the National Institute of Health (NIH) [1]) are an established method to evaluate and document the toxicities in clinical studies. CTCAE are a provider-based (clinicians or nurses) grading system, which facilitates the classification of adverse events (AEs) regarding their severity from mild to life-threatening to event-related death. During the last decades, the growing awareness of the importance to complement the traditional provider-rated assessment of the patient’s health status by patient-reported outcomes (PROs) triggered the development of valid and reliable instruments [2]. As “a measurement of any aspect of a patient’s health status that comes directly from the patient” [3] without being interpreted or altered by anyone else, PRO represents the gold standard to capture the patient’s perspective regarding his/her health status. PRO covers a wide range of both complex concepts such the patient’s functioning (physical, social, emotional, cognitive), depression, or anxiety as well as specific symptoms and overlaps strongly with CTCAE, especially with regard to the latter. Though the parallel collection of CTCAE and PRO ratings reflects a common practice in cancer clinical trials, their combination in order to maximize information yield is still uncharted territory.

Several studies found substantial discrepancies when it comes to comparisons of AE ratings from patients with those from providers. For non-observable symptoms such as fatigue or dyspnea, concordance of patient and clinician ratings was worse than for observable symptoms such as vomiting and diarrhea [4] and patients rated symptoms like fatigue, dyspnea, or skin toxicities more frequently and more severely than providers did [5–7]. Clinician ratings also lack sensitivity [2] and underestimate the severity of AEs [4]. A review of the literature on direct comparisons of PRO and CTCAE also reports that predominantly poor to moderate associations between clinical and patient-based AEs can be observed [8]. Thus, especially for those AEs, which can only be assessed via patients’ self-reports, the integration of PROs to collect information on AEs is a worthwhile strategy to improve this situation.

Besides the lacking concordance of patient-based and provider-based AE ratings, it is notable that even providers often achieve only moderate agreement. The CTCAE system itself has not undergone a formal validation procedure [5], and to the best of our knowledge, only two studies have investigated reliability of CTCAE ratings and reported only moderate rater agreement [9, 10].

Considering the abovementioned findings, integrating patient assessment with PRO measures into a multi-method strategy for AE identification may result in a substantial improvement of clinical trial methodology. To date, PRO and CTCAE ratings have been used in parallel rather than as a combined source for drug safety information. Integrating PRO data providing standardized information on toxicities into the process of CTCAE rating may increase inter-rater reliability as well as AE identification, in particular with regard to low-grade toxicity that is not related to salient clinical events such as unplanned hospitalization.

## Methods

### Trial objectives and endpoints

The trial aims at evaluating the impact of providing PRO data to providers on the accuracy of AE information, assessed by using CTCAE ratings. As there is no gold standard for AE ratings available, accuracy will be investigated in terms of inter-rater reliability.

The primary trial endpoint is the inter-rater reliability of CTCAE provider ratings for 17 AEs in cancer patients with mixed diagnoses. A superiority analysis will compare the inter-rater reliability between the control and the intervention groups for each assessed AE.

There are two secondary trial endpoints: (1) difference in the frequency of identified AEs (any grade) between the intervention and control group and (2) the comparison of the differences in inter-rater reliability between the intervention and control group across the different types of AEs.

The selection of CTCAE toxicities is based on the AEs detected by the European Organization for Research and Treatment of Cancer Quality of Life Core Questionnaire (EORTC QLQ-C30), which cover symptoms normally associated with chemotherapeutic treatments. In addition, AEs associated with immunotherapy have been added as this treatment option is becoming increasingly common in various diagnoses. The following 17 CTCAE toxicities will be assessed in this trial: anxiety, depression, irritability, concentration impairment, memory impairment, fatigue, pain, dyspnea, nausea, vomiting, insomnia, anorexia, diarrhea, constipation, peripheral sensory neuropathy, rash, and pruritus.

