### Trial procedure

During their day clinic or inpatient stay, all patients provide PRO data by autonomously completing questionnaires (EORTC QLQ-C30 and additional items from the EORTC Item Library) on a tablet PC. Subsequently, after having a medical encounter with the patient, two providers conduct consecutive, independent CTCAE ratings (intervention group: including PRO data, control group: no additional information). All data will be collected on the same day. Figure 1 depicts the trial flow, and Fig. 2 shows the Standard Protocol Items Recommendations for Interventional Trials (SPIRIT) figure [11].

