### Intervention

In the *control group*, providers use the assessment software to access and complete the CTCAE rating in an electronic format.

In the *intervention group*, providers see the respective patient’s PRO data next to the corresponding CTCAE domain, when accessing the rating. For an example of the CTCAE rating with and without displayed PRO data, see Fig. 3. In addition, providers can access the individual PRO questions and answers. This is especially important for subscales of the EORTC QLQ-C30, which comprise different CTCAE categories (e.g., the questions of the scale EORTC Emotional Functioning include the single CTCAE categories depression, anxiety, and irritability).

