### Statistical analysis

Only complete data sets will be used for final analysis. For analysis of the primary trial endpoint, we will compare inter-rater reliability of CTCAE ratings separately for each domain using intra-class correlation (ICC) coefficients. We would like to note that difference in ICC is an unusual endpoint, and to the best of our knowledge, no recommendations are available from the literature what constitutes a minimal important difference in ICC. According to Cicchetti [14], ICCs can be classified as follows: < 0.40 poor, 0.40–0.59 fair, 0.60–0.74 good, and > 0.75 excellent. This is consistent with the classification by Fleiss et al. [15].

For the analysis of the secondary trial endpoints, ICCs will also be compared across AEs to evaluate differences in the reliability of the CTCAE ratings across different types of AEs (e.g., AEs differing in observability). In addition to intra-class correlations, we will also compare percentage of absolute agreement of ratings and percentage for deviations by one and two grades. The frequency of identified AEs (any grade) will be compared between the intervention and control group using Fisher exact tests.

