## Discussion

Providing evidence for improved CTCAE ratings in cancer trials may have a substantial impact on how PROs are used in future trials and further strengthen the perceived relevance of the patients’ perspective (operationalized by using PRO measures) for outcome and safety assessment in cancer research. This may result in a new AE assessment strategy making combined PRO and provider ratings the new standard method. Naturally, enhanced AE assessment is beneficial not only in the context of clinical trials, but also with regard to daily oncological practice, cancer registries, and pharmacovigilance.

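### The aim is accuracy, but a gain in ICC can show only agreement, because the two raters share the PRO display in the intervention arm alone

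*Protocol article*

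**What the plan says.** The section Trial objectives and endpoints of the protocol article sets the aim: "The trial aims at evaluating the impact of providing PRO data to providers on the accuracy of AE information, assessed by using CTCAE ratings". It then gives the proxy and the reason for it: "As there is no gold standard for AE ratings available, accuracy will be investigated in terms of inter-rater reliability". The endpoint follows: "The primary trial endpoint is the inter-rater reliability of CTCAE provider ratings for 17 AEs in cancer patients with mixed diagnoses". Under Statistical analysis, "we will compare inter-rater reliability of CTCAE ratings separately for each domain using intra-class correlation (ICC) coefficients".

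Trial procedure describes the raters: "two providers conduct consecutive, independent CTCAE ratings (intervention group: including PRO data, control group: no additional information". Under Intervention, "providers see the respective patient’s PRO data next to the corresponding CTCAE domain, when accessing the rating". The Abstract (Methods) says the same for the intervention group: "providers see PRO results on the same screen as the CTCAE rating".

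The Discussion looks ahead to the conclusion: "Providing evidence for improved CTCAE ratings in cancer trials may have a substantial impact on how PROs are used in future trials". It goes on to suggest that combined patient and provider rating could become the standard approach.

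**The concern.** Agreement between two raters can stand in for accuracy when their errors are independent. What the raters share is then the patient's true state, and the ICC says how much of each rating reflects it. The intervention alters this condition. It gives both raters one further source, the patient's own PRO result, and any error in that source enters both ratings. The ICC cannot tell such shared error from true differences between patients. Because this happens in one arm only, the ICC does not measure the same thing in the two arms. Randomisation does not remove the difference, since the intervention itself produces it.

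The other analyses described do not fill the gap. Percentage agreement and deviation by one or two grades share the problem. The frequency of identified events is compared without any reference that is independent of the display. A positive primary result would therefore leave the stated aim unanswered, although the Discussion anticipates speaking of better ratings.

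**Working it through.** **The plan's own figure.** Power analysis gives 512 per group for q = 0.174, two-sided alpha 0.05, power 0.80. With the Fisher z comparison of two correlations, n = 2 × ((1.960 + 0.842)/0.174)² + 3 = 522 per group, 2.0% above the stated figure; power at 512 is 79.3%. The stated pair 0.40 vs 0.54 gives q = 0.604 − 0.424 = 0.181, close to 0.174. The sample size is reproduced within tolerance and is not affected by this point.

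**Model.** The documents give no variance components, so these are assumptions:

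- true severity T has variance 1;
- each provider's own error has variance 1.5, which puts the control ICC at 1/(1 + 1.5) = 0.40;
- the PRO equals T plus an error u, the same for both raters, with variance 1.5, so it is as noisy as one provider's rating;
- an intervention rating gives weight w to the PRO and 1 − w to the provider's own impression.

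Then, with V = Var(u):

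- ICC = (1 + w²V) / (1 + w²V + 1.5(1 − w)²)
- correlation with truth = 1 / √(1 + w²V + 1.5(1 − w)²)
- correlation that the ICC would imply if errors were independent = √ICC. In the control arm this is √0.40 = 0.63, equal to the actual value.

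**Varying the weight, V = 1.5.**

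| w | ICC | √ICC | actual correlation with truth |
|---|---|---|---|
| 0 (control) | 1/2.5 = 0.40 | 0.63 | 0.63 |
| 0.25 | 1.094/1.938 = 0.56 | 0.75 | 0.72 |
| 0.50 | 1.375/1.75 = 0.79 | 0.89 | 0.76 |
| 0.75 | 1.844/1.938 = 0.95 | 0.98 | 0.72 |
| 1 (copying) | 2.5/2.5 = 1.00 | 1.00 | 0.63 |

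From w = 0.5 to w = 1 the ICC keeps rising while accuracy falls back to the control value.

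**Varying the PRO error, w = 0.5.**

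| V | ICC | actual correlation with truth |
|---|---|---|
| 0 | 1/1.375 = 0.73 | 0.85 |
| 1.5 | 1.375/1.75 = 0.79 | 0.76 |
| 4.5 | 2.125/2.5 = 0.85 | 0.63 |
| 6.0 | 2.5/2.875 = 0.87 | 0.59 |

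At a fixed weight, a noisier PRO gives a higher ICC and a lower accuracy. Only with an error-free PRO does √ICC equal the actual correlation (√0.727 = 0.85). Simulation of 2,000 trials with 512 per arm agreed for V = 4.5 and V = 6.0, and ICC superiority was declared in every run, although accuracy was unchanged in the first case and lower in the second.

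**Would conditioning on the PRO settle it?** Given the PRO, the remaining variance of T at V = 1.5 is 1 − 1/2.5 = 0.6, so the conditional ICC is 0.6/(0.6 + 1.5) = 0.286 for every w below 1, and hence in both arms. It is 0.286 at w = 0.5 although accuracy has risen from 0.63 to 0.76. At w = 0.5 with V = 4.5 and V = 6.0 it is 0.353 and 0.364, again the same in both arms, although accuracy is unchanged in one case and falls in the other. Under full copying it is 0/0.

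**The case against.** The strongest reply is that the proxy is disclosed with its reason, that the Abstract already defines accuracy through reliability, and that the Discussion is hedged. Moreover, shared standardised information is the intervention, and the Background names higher reliability as the hoped-for effect, so the randomised ICC contrast estimates what was intended. The last part stands: the contrast is a valid estimate of the effect on agreement. The disclosure, however, covers only the use of a proxy. It does not say that the proxy behaves differently in the two arms.

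Three further objections limit how far the point can be taken, and all three stand.

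- A reader might infer that a positive result is close to built in. The documents do not support that. Providers grade against CTCAE definitions in connection with a medical encounter, no ready-made CTCAE grade is displayed, some PRO scales span several CTCAE terms, and each provider does the mapping without special training. The weights are assumptions.
- A reader might infer that ratings will become no more accurate. In the model with V = 1.5, accuracy exceeds control at every weight strictly between 0 and 1. To leave it unchanged at w = 0.5 the PRO error variance must be three times the provider's (4.5 against 1.5).
- Control errors are not shown to be independent either. Both control raters assess the same patient on the same day, so misreporting by the patient can be shared there as well. The model sets this to zero and so exaggerates the contrast. The intervention still adds a shared source that the control arm lacks.

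**Conclusion.** The point holds in a limited form. The primary contrast supports a conclusion about inter-rater agreement and cannot by itself support one about accuracy. In the illustration with half weight, an ICC of 0.79 would be read as a correlation with truth of 0.89 when it is 0.76, and under full copying an ICC of 1.00 goes with no gain at all (0.63 in both arms). These sizes rest on assumed variances, an assumed weight and independent control errors; the direction of the distortion needs only that the PRO carries some error and that both intervention raters use it. Nothing here shows that accuracy will fail to improve, and the sample size is untouched. A reader might also expect the ICC conditional on the PRO to separate copying from better assessment. It does not: it is equal in both arms whether accuracy rises, stays or falls.

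**What to change.** In the Abstract (Background), in Trial objectives and endpoints, and in the Discussion, restate the aim and the intended conclusion as inter-rater agreement (reliability) of CTCAE ratings. Add one sentence under Trial objectives and endpoints: because both intervention-arm raters see the same PRO data, a gain in ICC alone will not be reported as better accuracy or as improved ratings.

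An ICC conditional on the corresponding PRO score may be reported for each adverse event, but only descriptively, as the part of agreement that does not run through the PRO. It should not be presented as a test of copying against better assessment. Its absence from the article is not a fault, since the analysis plan may cover it. Performance status and concurrent medication, which the case report form collects, are too weak as references for terms such as pruritus or memory impairment.

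The change is one of wording, with no new data and no new sample size. The cost is a narrower headline claim. Keeping an accuracy claim would instead require a reference independent of the display, for example a blinded structured assessment in a subsample, which is a change of design.

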### Power analysis

A sample size of 1024 patients (512 per group) allows to detect differences in ICC with an effect size of *q* = 0.174 (alpha = 0.05, beta = 0.20, two-sided). This effect size corresponds to differences in reliability of, e.g., 0.20 vs 0.36, 0.40 vs 0.54, or 0.60 vs 0.70. Power analysis for ICC has been approximated by Pearson correlation coefficients as suggested by Streiner et al. [16]. The planned sample size is sufficient to detect a difference corresponding to about half a category width in this classification.

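### Seventeen co-equal primary ICC comparisons rest on a sample size computed for one test at an undivided two-sided alpha of 0.05, and the article states no multiplicity adjustment or success rule

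*Protocol article*

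**What the plan says.** Under Trial objectives and endpoints, the Protocol article sets one primary endpoint: "The primary trial endpoint is the inter-rater reliability of CTCAE provider ratings for 17 AEs in cancer patients with mixed diagnoses". The next sentence reads: "A superiority analysis will compare the inter-rater reliability between the control and the intervention groups for each assessed AE". The Statistical analysis section repeats the structure: "we will compare inter-rater reliability of CTCAE ratings separately for each domain using intra-class correlation (ICC) coefficients".

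The only error rates for these comparisons are in the Power analysis section. It gives "A sample size of 1024 patients (512 per group") as sufficient to detect "differences in ICC with an effect size of *q* = 0.174", with "alpha = 0.05, beta = 0.20, two-sided". It illustrates this by "differences in reliability of, e.g., 0.20 vs 0.36, 0.40 vs 0.54, or 0.60 vs 0.70" and describes the detectable difference as roughly half the width of one reliability class.

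The article does not name a leading AE, a testing order, a pooled ICC, a multiplicity method or a number of AEs that must differ. It does not call the AE-specific comparisons exploratory. The Discussion part of the Abstract and the main Discussion both anticipate a general conclusion: that patient-reported data improve CTCAE rating reliability and may change how adverse events are assessed.

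**The concern.** Seventeen superiority comparisons share primary status, and the sample size gives each the full 5%. If the tests are run at that level, a false significant result somewhere among them becomes likely even if the display changes nothing. Without a success rule, the reader of the results cannot tell whether one, five or all 17 significant AEs would support the general conclusion.

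The sample size is tied to the same choice. If an adjustment is added later, the stated detectable effect no longer holds at 80% power. So the article's power statement and control of the family-wise error cannot both stand as written.

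**Working it through.** **Inputs.** 17 comparisons (Trial objectives and endpoints). 512 per group, q = 0.174 as a difference of Fisher z values, two-sided alpha 0.05 and power 0.80 (Power analysis). That section also states: "Power analysis for ICC has been approximated by Pearson correlation coefficients". Correlations between the 17 test statistics are not given; the values below are assumptions.

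**1. Reproducing the plan's figure.** For two independent correlations:

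- n per group = 2 × ((1.960 + 0.842)/0.174)² + 3 = 522, against 512 stated (1.9% apart).
- Standard error of the z difference at 512 per group = √(2/509) = 0.0627.
- Power at q = 0.174 = Φ(0.174/0.0627 − 1.960) = Φ(0.816) = 79%.
- A one-sided 0.05 test would give a detectable q of 0.156, which does not match.

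So the stated size belongs to one comparison at undivided two-sided 0.05.

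**2. Family-wise error with all 17 nulls true, each tested at two-sided 0.05.**

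- Any false difference, independent tests: 1 − 0.95^17 = 58.2%.
- A false difference favouring the intervention (0.025 per test), independent tests: 1 − 0.975^17 = 35.0%.
- Expected false positives: 17 × 0.05 = 0.85 in either direction, and 17 × 0.025 = 0.43 favouring the intervention.

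With equicorrelated normal test statistics (numerical integration):

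| Assumed correlation | Either direction | Favouring intervention |
|---|---|---|
| 0 | 58.2% | 35.0% |
| 0.1 | 56.8% | 31.7% |
| 0.3 | 49.3% | 25.4% |
| 0.5 | 38.6% | 19.4% |
| 0.7 | 27.1% | 13.5% |

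As a check, two-rater ICC differences were simulated with normal ratings, a true ICC of 0.5 and 512 per group. Correlations of 0.3 to 0.5 between AEs and between rater errors gave test-statistic correlations of about 0.09 to 0.26. The error was then 53–57% in either direction and 27–32% favouring the intervention.

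**3. What adjustment does to the power statement.** Bonferroni is used as the illustration; it is also the first step of Holm.

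- Level per test = 0.05/17 = 0.0029, critical value 2.974.
- Power at q = 0.174 = Φ(2.776 − 2.974) = Φ(−0.198) = 42%.
- q detectable with 80% power = (2.974 + 0.842) × 0.0627 = 0.239, i.e. 0.20 vs 0.42, 0.40 vs 0.58, or 0.60 vs 0.73.
- Keeping 80% power at q = 0.174 would take 965 per group, 1930 in total.

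**4. The class-width statement.** The cut-points in Statistical analysis put the fair class at about 0.20 wide and the good class at about 0.15.

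- Unadjusted, the plan's examples cover 0.14/0.20 = 70% and 0.10/0.15 = 67% of those classes, and 0.16/0.40 = 40% of the poor class. About half is a loose summary of these.
- Adjusted, the same starting points need 0.18/0.20 = 90% and 0.13/0.15 = 87%, and 0.22/0.40 = 55% for the poor class. For the fair and good classes, the statement no longer describes what the trial can detect.

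**The case against.** There are three serious arguments on the other side.

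**The analysis plan may deal with it.** This is a condensed article, the analysis plan is not shown, and multiplicity is commonly left to that plan. The Statistical analysis section gives no significance level for the ICC comparisons; 0.05 appears only in the power calculation. This stands in part: one can say only that no adjustment is stated here, not that none will be made. It does not remove the point, because any adjustment would contradict the detectable effect the article already states.

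**The claims may be AE-specific.** If each AE is its own question, each test carries its own 5%, and family-wise control over 17 distinct symptoms is open to debate. The figure q = 0.174 is correct as a per-AE figure. But the article draws a general conclusion and already assigns differences between AE types to a secondary endpoint, so the primary comparisons have to carry the overall claim. A reader might infer that one significant AE would be declared trial success. No such rule is written; the defect is that no rule is written at all.

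**The error can be overstated.** A reader might infer a 40–58% chance of a false superiority claim. The documents do not support that. Those percentages count false differences in both directions, and the lower end needs an assumed correlation of about 0.5. A false result favouring the intervention has probability at most about 35%.

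**Conclusion.** The point holds in this form: 17 co-equal primary comparisons, a sample size built on undivided alpha for one of them, and no adjustment, key AE or success rule stated in this article.

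If all nulls are true and each test is run at two-sided 0.05, the chance of a false result favouring the intervention is about 19–35% for correlations from 0.5 down to 0. That is roughly 8 to 14 times the nominal 2.5% in that direction. For any false difference the corresponding range is about 39–58%. The upper ends are exact under independence; the lower ends rest on an assumed common correlation.

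The sample size is arithmetically sound for what it computes. It supports the stated detectable effect only while the tests remain unadjusted. The 42% power under adjustment applies to Bonferroni and to Holm's first step; Holm would recover some power if many AEs truly improve. This should be settled before results are seen, because it determines what the primary endpoint can claim.

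**What to change.** 1. In Statistical analysis, state that family-wise error over the 17 primary ICC comparisons is controlled at two-sided 0.05, for example by Holm, before superiority is claimed for any AE.
2. In Power analysis, state that q = 0.174 is an unadjusted per-AE figure. Add that at 0.05/17 with 512 per group its power is about 42%, and that the effect detectable with 80% power is about q = 0.24 (0.40 vs 0.58, 0.60 vs 0.73). Limit the class-width remark to the unadjusted case.
3. State what result would support the general conclusion. One option is a single pre-specified global test of the mean Fisher-z ICC difference over the 17 AEs. Its standard error is 0.0627 × √((1 + 16ρ)/17) if all AEs have equal precision. Multiplied by 2.802, this gives a detectable mean q of about 0.04 at ρ = 0 and 0.13 at ρ = 0.5.

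**Cost.** Items 1 and 2 are changes of wording and need no extra patients; the price is a larger detectable difference for each AE. The global test is a choice, not a requirement. It changes the primary question, and averaging may dilute a gain confined to a few AEs. If it is run as a permutation test it should be studentised, because the display may also change how often AEs are recorded, and the permutation null is broader than equal ICCs.
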